**A.- Introduction and hypothesis**

Pterygium is a benign tumor growing in the conjunctiva and the cornea resulting in obvious problems for patients´ sight. Histologically, the lesion is characterized by metaplasia of the squamous epithelium, goblet cell hyperplasia and abnormal expression of p53. Under the epithelium, the connective tissue contains numerous fibroblasts and blood vessels. The malignant cells express large amounts of factors which result in increased angiogenesis and migration capabilities, these include VEGF, versican, TGF, IL-6, and IL-8, among others (Di Girolamo et al. Pathogenesis of pterygia: role of cytokines, growth factors, and matrix metalloproteinases. Prog. Retin. Eye Res. 2004; 23:195-228).

The usual therapy includes the surgical resection of the lesion, but the percentage of relapses is very high. If a second intervention is needed, this may cause serious vision problems due to the formation of scar tissue and other side effects (Dushku et al. Pterygia pathogenesis: corneal invasion by matrix metalloproteinase expressing altered limbal epithelial basal cells. Arch. Ophthalmol. 2001; 119:695-706).

Doxycycline is a bacteriostatic antibiotic that has been used in the clinic for decades. It has been shown that doxycycline is able to block angiogenesis through a metalloproteinase inhibition mechanism which is independent of its antimicrobial activity (Dan et al. Inhibitory effect of oral doxycycline on neovascularization in a rat corneal alkali burn model of angiogenesis. Curr. Eye Res. 2008;33:653-660).

In a recent experiment, using an animal model of pterygium in vivo, it was shown that doxycycline by itself was able to eliminate pterygium in mice with a 100% efficacy (Cox et al. Doxycycline´s effect on ocular angiogenesis: an in vivo analysis. Ophthalmology, in press).

The hypothesis we are trying to test in this study is that a doxycycline treatment may be able to reduce pterygium growth in patients. In case the lesions are totally eliminated, as happens in mice, the benefits would be obvious for both the patients and the Health system, since surgical interventions would be reduced with all the implications in patients´ safety, and economic savings in operating room occupation and running costs. If the reduction were partial, then doxycycline could be used to delay surgery when needed.

Therefore, this a hypothesis of superiority of the doxycycline treatment versus a placebo in the growth of pterygium.

This is the first time doxycycline is used in humans to treat pterygium.

**B.- Clinical Trial Design**

The study has been designed as a unicentric trial, to be carried out at the Hospital San Pedro, Logroño (La Rioja), Spain. Two groups will be studied, one will receive doxycycline (2 daily doses, 100 mg each) for 30 days, while the other will receive a placebo. Patients will be randomly assigned to one of the two arms following a 1:1 proportion (treatment:placebo). Masking will be done using a double blind technique, so neither the patient nor the doctor will know who is receiving doxycycline or placebo.

To complete the study, each patient will be asked to attend 4 visits to the clinic, as follow:

Visit 1. Clinical history data will be collected and the lesion will be properly diagnosed. If the patient meets the inclusion criteria and does not fulfil any of the exclusion criteria, he/she will be asked to participate in the trial and sign the informed consent form. Consenting patients will be given a code for identification throughout the study. A photograph of the affected eye (or both in bilateral lesions) will be taken. The Pharmacy of the Hospital will provide the patient with a capsule bottle (randomly assigned to his/her study code containing either doxycycline or placebo) and the proper instructions to take the medicine together with instructions for following visits and telephone numbers for potential adverse affects.

If a patient needs to be excluded or does not consent to be included in the study, he/she will be asked for informed consent to use cells from his/her resected pterygium for experiments on cell and molecular biology. All regular procedures will be followed with these patients.

Visit 2. This will happen 31 days alter the first visit. The degree of compliance will be evaluated and the number of capsules that were not taken for any reason will be recorded. A second photograph of the affected eye(s) will be taken to compare with that taken in the first visit. The ophthalmologist will again evaluate the lesion and, depending on the stage of this lesion, a decision will be taken to remove it or not, following the usual protocols set in place by the Ophthalmology Service. If the pterygium is removed, the tissue will be sent to the CIBIR for cellular and molecular analyses.

Visit 3. It will take place 6 months alter the second one. The doctor will recognize the patient and record his/her observations. Particular care will be devoted to annotate any recurrences.

Visit 4. It will take place 6 months alter the third one. The doctor will recognize the patient and record his/her observations. Particular care will be devoted to annotate any recurrences.

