**F.-** **Statistical analysis**

The variables that will be statistically analyzed are, on the one hand, the growth or reduction of the surface occupied by the pterygium lesion after the treatment as compared with that before the treatment. In addition, the recurrence percentage in both arms and the expression of genes and proteins in pterygium cells either treated or not with doxycycline will be analyzed. First, normalcy of distribution and variance of the data will be checked. If data are distributed normally and present homoscedasticity, comparison between both groups will be performed with simple tools such as Student´s *t* test. Otherwise, non-parametric tests will be used. Differences will be considered statistically significant when *p*<0.05. All patients that return to their second visit will be included in the analysis (intention to treat analysis).

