**H.-** **Security and ethical considerations**

Doxycycline is drug with a very high security profile and very well known.

A short-term treatment with doxycycline has very low risks since this drug has been used for decades in the clinic (Brandt et al., Effects of doxycycline on progression of osteoarthritis. Results of a randomized, placebo-controlled, double blind trial. Arthritis Rheum. 52:2015-2025; 2005). If the treatment works in a similar way to what was observed in mice, patients could benefit from a reduction in their pterygium lesion, being even able to postpone their surgical intervention.

In patients receiving placebo no benefits are expected but no major damages are expected either, since the only think we ask is for their surgical intervention to be delayed for 4 weeks. In this period the expected growth of the lesion is minimal.

No vulnerable populations will be included.

No economic compensations are contemplated.

All the information that will be given to the patients, their family, and legal representatives is collected in the Information to Patients Document.

No additional explorations will be needed. The habitual care for pterygium patients will be applied to all participants.

All monitorizations, audits, revisions by the Local Committee for Clinical Research, and regulatory inspections related to the study will be allowed, facilitating direct access to original documents and data.

Placebo will be used as a control since no pharmacological treatment has been approved for the treatment of pterygium.

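### The protocol specifies no systematic adverse-event enquiry, so tolerability in the two masked arms would rest on patient-initiated telephone calls

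*Protocol*

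**What the plan says.** **Visit 1 (Protocol, section B).** Patients leave with their capsules and "instructions for following visits and telephone numbers for potential adverse affects". No step for recording such calls is described.

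**Visit 2 (section B), 31 days after Visit 1.** "The degree of compliance will be evaluated and the number of capsules that were not taken for any reason will be recorded". A second photograph is taken and the lesion is evaluated again. Section G describes the same visit as registering compliance information and taking the photograph.

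**Visits 3 and 4 (section B), 6 and 12 months after Visit 2.** "The doctor will recognize the patient and record his/her observations", and "Particular care will be devoted to annotate any recurrences".

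**Outcomes and analysis.** Section C names the lesion-area ratio as the main outcome, with recurrence at 12 months and gene and protein expression as secondary outcomes. Section F begins with the change in lesion surface, then lists the further variables to analyse, in a sentence cut here before its final verb: "In addition, the recurrence percentage in both arms and the expression of genes and proteins in pterygium cells either treated or not with doxycycline will". It restricts the analysis to patients who return for Visit 2. No safety variable appears in either section.

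**Safety position.** Section A ends: "This is the first time doxycycline is used in humans to treat pterygium". Section H states: "Doxycycline is drug with a very high security profile and very well known". Sections D and H support this with long general use and a placebo-controlled trial in osteoarthritis. Section D adds that the same dosage, given for up to 30 months, produced few and moderate adverse effects.

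**The concern.** Section A presents doxycycline as a way to avoid or delay surgery on a benign lesion. That calls for weighing benefit against harm. The trial has a masked placebo arm, which is the best means of separating drug effects from background complaints, but the plan has nobody ask the patients.

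Two features add to this. First, the capsule count covers omissions for whatever cause, and the text does not say whether the cause is noted. On the count alone, a patient who stopped because of an adverse effect looks the same as one who forgot. Second, a patient who stops for that reason and does not return for Visit 2 is outside the analysed set and leaves no stated trace.

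The loss is hard to repair. Visit 3 comes 6 months after Visit 2, which is late for reliable recall of a 30-day course.

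**Working it through.** **1. Where adverse events could enter the data**

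| Place in protocol | Content listed | Adverse-event enquiry |
| --- | --- | --- |
| B, Visit 1 | Telephone numbers handed out | Patient-initiated only, no recording step |
| B, Visit 2; G | Compliance, untaken capsules, photograph, lesion evaluation | None listed |
| B, Visits 3 and 4; G | Doctor's observations, recurrences | None listed |
| C | Area ratio, recurrence, expression | No safety outcome |
| F | Lesion surface, recurrence, expression | No safety variable |
| H | General safety statements | No recording, grading or reporting set up |

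**2. The plan's own sample size.** Section E assumes a difference of 15 − 5 = 10 points, SD 15 and a two-sided 5% level. The normal approximation at 90% power gives 2 × (1.960 + 1.282)² × 15²/10² = 47.3, so 48 per group. The exact t-test calculation gives 49, with power 0.904. The stated 49 per group is reproduced and is used below.

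**3. What 49 patients per arm would show if all were asked.** The documents give no adverse-event rates, so the true rates p here are assumptions. The probability of seeing at least one case in an arm is 1 − (1 − p)^49.

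| True rate p | Probability of at least one case |
| --- | --- |
| 1% | 0.39 |
| 2% | 0.63 |
| 5% | 1 − 0.95^49 = 0.92 |
| 10% | 0.99 |

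With zero events in 49, the one-sided 95% upper bound is 1 − 0.05^(1/49) = 0.059, or 5.9%.

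**4. What incomplete reporting does to those statements.** Let f be the share of affected patients who telephone. It is unknown; take f from 30% to 100% as an assumed range.

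- Probability that a 5% event becomes known at least once: 1 − (1 − 0.05f)^49. At f = 1 this is 0.92; at f = 0.30 it is 1 − 0.985^49 = 0.52.
- Upper bound on the true rate after no calls: 0.059/f. At f = 1 this is 5.9%; at f = 0.30 it is 0.059/0.30 = 0.198, or about 20%.

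With calls alone f is not known, so neither statement can be made with a definite figure.

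**5. Comparison between arms.** Assume true rates of 15% on doxycycline and 5% on placebo. Expected affected patients are 49 × 0.15 = 7.4 and 49 × 0.05 = 2.5. If 30% call in each arm, 7.4 × 0.30 = 2.2 and 2.5 × 0.30 = 0.7 are known. The ratio stays near 3:1 but the counts become very small.

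Full collection would not give much power either. With 49 per arm and a two-sided 5% level, placebo rates of 5%, 10% and 20% need doxycycline rates of about 25%, 33% and 47% for 80% power. The 15% versus 5% case has power of only about 0.38 by the normal approximation for two proportions: [0.10 − 1.96 × √(2 × 0.10 × 0.90/49)] / √[(0.15 × 0.85 + 0.05 × 0.95)/49] = −0.31, and Φ(−0.31) = 0.38.

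**The case against.** The strongest defence has four parts.

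**The visit lists need not be exhaustive.** Doctors record observations at Visits 3 and 4 without a stated limit. At Visit 2 the degree of compliance is evaluated as well as counted, and section G speaks of compliance information more broadly. This stands in part. A reader might infer that reasons for missed capsules are excluded, but the text is only silent on them. A careful site may well ask. The plan does not make it do so, or do so in the same way for every patient.

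**Voluntary reports are still comparable.** A reader might infer that harm cannot be compared at all, or that the calls lack a denominator. Neither is supported. Every patient dispensed a bottle gets the telephone numbers, so the denominator exists. Under masking the documents give no reason for calling rates to differ by arm. The weakness is incomplete ascertainment of unknown extent.

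**Full collection would rarely separate the arms.** This stands, as step 5 shows. It argues for a descriptive table, not for leaving the question out.

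**The drug is well known.** This also stands. A reader might take the first-use sentence in section A to mean that the drug's safety is unknown. That sentence concerns the indication, and sections D and H describe extensive earlier use. This lowers the stakes, but the cited experience is not in pterygium patients.

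It could also be said that the missing analysis plan may cover safety. It could supply a table, but not answers to questions the protocol never has anyone ask.

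**Conclusion.** The point holds as a gap in data collection. No visit description includes an adverse-event enquiry, and no safety variable is among the outcomes or analysed variables. Following the protocol as written leaves patient-initiated reports only, and so no systematic basis for describing or comparing tolerability.

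What is lost is mainly a description: the 92% chance of seeing a 5% event and the 5.9% upper bound, both of which require that all 49 patients in an arm are asked. Little formal comparative power is lost, because 49 per arm offers little. The 15%, 5% and 30% figures are assumptions for scale, and the conclusion does not depend on them.

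Nor is Visit 2 the only contact after treatment, as a reader might infer; Visits 3 and 4 follow. It is the only visit close to the end of dosing. The appropriate label is a cheap improvement.

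**What to change.** - **Section B, Visit 2:** add a standard open question on adverse events since Visit 1, asked while patient and doctor are still masked, and record the answer for every patient.
- **Section B, Visit 2:** beside the capsule count, record the reason for capsules not taken, with adverse event as one category.
- **Patients who miss Visit 2:** ask the same questions by telephone, so that those who stopped and stayed away are not lost.
- **Sections C and F:** state that the number of patients per arm with any adverse event, with any serious event, and stopping because of an adverse event will be reported descriptively, over all patients dispensed a bottle. Because power is low, no formal test is needed, and the absence of a significant difference should not be read as equal safety.

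The cost is a few minutes of recording at a visit already held, a call to each non-returner and one table. Sample size, treatment and primary analysis are unchanged.

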**C.-** **Objectives and outcome endpoints**

The main objective of the study is to reduce pterygium growth with a pharmacological treatment and reduce the Lumber of cases that need surgical resection of the lesion.

As secondary objectives we look forward to:

1.- Determine whether treatment with doxycycline reduce recurrence rates in patients whose pterygium was surgically removed.

2.- Investigate which genes and/or proteins change their expression following treatment of pterygium cells with doxycycline.

To accomplish these objectives, a photograph of the lesion(s) will be taken Turing the first visit. After 30 days of treatment, a second photography of the same area will be taken. The surface occupied by the lesion will be calculated in both photographs using an image analyzing software package. The main outcome will be the ratio between the surface occupied by the lesion in the second photograph divided by the size in the first one (growth rate).

As secondary outcomes, we will analyze the recurrence rate at 12 months after the intervention and the genomic/proteomic expression of the resected pterygium.

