**G.-** **Proposed time table**

Each specific patient will remain formally in the study for 13 months. In the first visit all pertinent data will be collected and he/she will be informed of the study´s dynamics. A photograph of the affected eye(s) will be taken in this first visit and the patient will receive a bottle with 60 capsules that need to be taken during the following 30 days. After this period, a second visit will take place where information regarding compliance with the treatment will be registered. In addition, a second photograph of the lesion(s) will be taken. After this, surgical resection of the pterygium will be performed in those patients that need it in accordance with the protocols of the Ophthalmology Service. All procedures will be done in the same way and by a maximum of 2 ophthalmologists. Two more visits will be scheduled at 6 and 12 months after the second one. In these sessions, the evolution of the lesion will be recorded and special attention will be paid to potential recurrences, in which cases the protocols of the Ophthalmology Service will be followed.

As it pertains to the whole study, 18 months seem to be enough to recruit the needed 98 patients. If we add the 13 months needed for the last patient to complete his/her follow-up, the study could close 31 months after it opens. We propose initiating the study on February 2009 and closing up on August 2011.

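### Recurrence is compared only among operated patients, a group formed after 30 days of study drug, so randomisation does not protect that secondary comparison; the 12-month time point also conflicts with the visit schedule

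*Protocol*

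**What the plan says.** Section C gives the recurrence objective: "Determine whether treatment with doxycycline reduce recurrence rates in patients whose pterygium was surgically removed". The population is therefore the operated patients.

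Section B says how that population arises. At visit 2, 31 days after visit 1, the ophthalmologist re-examines the lesion and, "depending on the stage of this lesion, a decision will be taken to remove it or not", following the Ophthalmology Service's usual protocols.

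The main objective in section C is to "reduce pterygium growth with a pharmacological treatment and reduce the Lumber of cases that need surgical resection of the lesion". The drug is thus intended to change both the lesion and the number of operations.

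Section F lists "the recurrence percentage in both arms" among the analysed variables, with significance at p<0.05. It adds: "All patients that return to their second visit will be included in the analysis (intention to treat analysis". It does not say how patients without surgery enter the recurrence comparison.

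On timing, section C states that "we will analyze the recurrence rate at 12 months after the intervention". Section G states "Two more visits will be scheduled at 6 and 12 months after the second one", and section B spaces visits 3 and 4 in the same way. Section G places surgery after visit 2 without an interval: "After this, surgical resection of the pterygium will be performed in those patients that need it".

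**The concern.** Randomisation makes the arms comparable at visit 1. It does not make comparable those patients in each arm who are later selected on something the treatment may have altered. If doxycycline shrinks some lesions enough to avoid surgery, its operated patients are those with the more severe or less responsive lesions, while the operated placebo patients remain a broader mix. If severity also raises the risk of recurrence, the operated doxycycline patients recur more often even when the drug does nothing to recurrence. A drug that succeeds on the main objective could then be reported as worsening recurrence, or a real benefit could be hidden.

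Recurrence is the only clinical outcome among the secondary ones, and section A presents relapse after surgery as a central problem, so readers will give the result weight.

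The timing is a separate question. A 12-month endpoint counted from surgery cannot be read exactly from a visit counted from visit 2 unless the operation takes place on the day of visit 2.

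**Working it through.** **The plan's own figure.** The protocol gives no figure for recurrence. Its only sample size for the 10-point difference concerns the primary outcome (section E: difference 10, SD 15, two-sided 5%). The normal formula n = 2(z₀.₉₇₅ + z_power)² SD²/difference² gives:

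- 90% power: 2 × (1.960 + 1.282)² × 225/100 = 47.3, so 48 per arm (49 by the noncentral t). The protocol has 49.
- 80% power: 2 × (1.960 + 0.842)² × 225/100 = 35.3, so 36 per arm (37 by the noncentral t). The protocol has 35.

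The figures agree within 2 patients, but they say nothing about recurrence in a subset.

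**Selection, by simulation. Every input here is an assumption.** Severity S is standard normal. Stage at visit 2 is S − δ × (doxycycline) + noise with SD 0.5. Surgery takes place if stage exceeds −0.5. The logit of recurrence is logit(0.3) + log(OR) × S, with no term for the drug. Any difference in recurrence between arms is therefore spurious.

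| Shift δ (SD of S) | Operated, placebo vs doxycycline | OR per SD | Recurrence in operated, placebo vs doxycycline | Spurious excess (points) |
|---|---|---|---|---|
| 0 | 67% vs 67% | any | equal | 0 |
| 0.1 | 67% vs 64% | 2 | 38.0% vs 38.7% | 0.6 |
| 0.3 | 67% vs 57% | 2 | 38% vs 40% | 2.0 |
| 0.5 | 67% vs 50% | 2 | 38% vs 42% | 4 |
| 1.0 | 67% vs 33% | 2 | 38% vs 46% | 8 |
| 0.5 | 67% vs 50% | 1.5 | 34% vs 37% | 2 |
| 1.0 | 67% vs 33% | 3 | 43% vs 55% | 12 |

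A second model, with placebo surgery of 60% to 90% and reductions of 10 to 40 points, gives spurious odds ratios of 1.05 to 1.60, all against doxycycline.

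**Bounds that do not use a severity model.** Assume 80% of placebo and 60% of doxycycline patients are operated, the drug only ever prevents surgery, and recurrence among operated placebo patients is 30%. The share of operated placebo patients who would be operated in either arm is 60/80 = 75%. Their placebo recurrence is known only to lie between (0.30 − 0.25)/0.75 = 7% and 0.30/0.75 = 40%. The data alone cannot say which value should be set against the doxycycline arm.

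**Size against noise.** With 49 per arm and surgery of 67% vs 50%, about 33 and 24.5 patients are operated. The standard error of the difference is √(0.38 × 0.62/33 + 0.416 × 0.584/24.5) = 13 points. At 67% vs 33% (33 and 16 operated) it is 15 points.

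**All-randomised measure.** In the same model at OR 2, the proportion operated and recurring is 0.67 × 0.38 = about 26% on placebo, against 0.50 × 0.416 = 21% (δ = 0.5) or 0.33 × 0.46 = 15% (δ = 1.0) on doxycycline. It falls although the drug does not act on recurrence, because fewer patients are operated.

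**Timing.** Visit 4 is visit 2 + 12 months, and surgery is visit 2 + d. Follow-up after surgery at visit 4 is 12 − d months. It equals 12 only if d = 0, and the protocol does not give d.

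**The case against.** The strongest reply is that the bias is conditional and may be small. It needs doxycycline to change who is operated, yet surgery also follows the service's usual protocols, and the planned effect is only 10 points of lesion area with no stated link to surgery rates. Shifts of 0.1 to 0.3 SD produce 0.6 to 2.0 points at OR 2. The 4- and 8-point cases are about 0.3 and 0.5 of a standard error. The 12-point case needs surgery halved and OR 3 together. All of this stands. It limits the size that can be claimed, but it does not restore comparability, and fewer operations is part of the effect the trial hopes to show. Masking keeps knowledge of the arm out of the surgical decision, but not the effect of the drug on the lesion.

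A further reply is that section F alone does not restrict the recurrence percentage to operated patients. That is correct: the restriction comes from the objective in section C.

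An all-randomised composite can also be criticised because it does not answer objective 1 and improves when only surgery falls. That stands too, and governs how it may be read.

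A reader might infer three stronger things that the documents do not support:

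- **The visit 2 clock itself breaks randomisation.** It does not: visit 2 is a common origin for both arms. Moreover, the outcome is defined from the intervention, a word that sections A and H use for surgery, and only the visit schedule runs from visit 2.
- **Every operated patient is followed for less than 12 months.** This fails for anyone operated on the day of visit 2, and the interval is not stated.
- **Doxycycline patients will be operated later.** Section H mentions postponement only as something that could follow if the drug works as in mice.

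**Conclusion.** The concern holds for the secondary recurrence comparison. The operated group is formed after randomisation on a lesion stage that the drug is meant to change, so a difference in recurrence between operated patients by arm cannot be attributed to doxycycline on the strength of randomisation. If severity drives both surgery and recurrence and the drug reduces surgery, the bias runs against doxycycline.

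Its size cannot be derived from the protocol. The range of about 1 to 12 points illustrates assumed surgery rates and severity effects; it is not an estimate for this trial, and the bias is zero if the drug leaves the choice of operated patients unchanged.

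The conflict between the two 12-month time points is a separate and smaller matter of reconciliation. The primary outcome compares photographs from visits 1 and 2, before the visit 2 surgical decision is carried out, and is untouched. As the point concerns a secondary outcome, it calls for a correction to the plan but does not threaten the main conclusion.

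**What to change.** 1. **Label the operated-only comparison** as non-randomised and exploratory, adjust it for baseline lesion area, and draw no causal claim from it. Adjustment removes only the part of the selection that baseline area captures.
2. **Add a comparison over all randomised patients**: the proportion with surgery followed by recurrence by visit 4, as a risk difference with 95% confidence interval. Always show the proportion operated beside it, and read the result as combined surgical burden, not as an effect on recurrence.
3. **Reconcile the time point** in section C with the visits in sections B and G. Record the date of surgery and analyse recurrence by time from that date, censored at the last visit.

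The cost is protocol wording, a second denominator and one date per operated patient; no extra visit is needed. The small downside is that the all-randomised measure mixes need for surgery with recurrence, which is why its components must be shown with it.

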**E.-** **Patients**

**Total Lumber of patients**

There are 2 ways of calculating sample size to reach statistical significance in a clinical trial. The first one is a qualitative strategy where each patient is classified as a success or a failure to the treatment depending on whether their lesion size shrinks below a predetermined value (threshold). This allows a comparison between groups using a bilateral 2 for 2 independent samples. From the study of the disease we know that untreated pterygia keeps growing or maintains its size, but never tends to spontaneously reduce its size, so we can assume that the proportion of the placebo-treated group is asymptotically 0.0%. Depending of the power and the established threshold, the number of patients for each group are the following:

| **Power** | **Treshold at 25%** | **Treshold at 50%** | **Treshold at 75%** | **Treshold at 100%** |
| --- | --- | --- | --- | --- |
| 80% | 27* | 11 | 6 | 1 |
| 90% | 35 | 14 | 7 | 2 |

* Numbers indicate sample size on each group.

Secondly, we can also use a quantitative strategy where each patient receives a numeric value representing the percentage reduction (or growth) of his/her pterygium due to treatment. In this case, to detect significant differences in the null hypothesis contrast Ho:1=2 we will use a bilateral Student´s *t* test for 2 independent samples. If we assume that the mean reduction of the lesion in the placebo group is 5 % and in the doxycycline-treated group is 15 %, and that the standard deviation in both groups is a maximum of 15%, for a significance levels of 5%, the number of subjects is as follows:

| **Power** | **Number of patients per group** |
| --- | --- |
| 80% | 35 |
| 90% | 49 |

Since it is difficult to forecast the expected response, we have decided to follow the most stringent conditions and 98 patients will be recruited (49 treated with doxycycline and 49 treated with placebo). This sample size will allow to detect significant differences of 10% or higher in the diminution of pterygium size between the treated and the placebo groups. Besides, this number of patients will allow the qualitative analysis previously explained.

Recruitment will be performed among patients attending the Ophthalmology Service of the Hospital. Currently, 4 to 8 pterygium patients visit the Hospital every month.

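### The primary comparison of the post/pre area ratio makes no adjustment for baseline lesion area: the test is valid, but it gives up precision that data already collected could supply

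*Protocol*

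**What the plan says.** - Section C (Objectives and outcome endpoints) sets the main outcome: "The main outcome will be the ratio between the surface occupied by the lesion in the second photograph divided by the size" in the first photograph.
- Section E (sample size, quantitative strategy) gives each patient one number, the percentage change of the lesion, and states "we will use a bilateral Student´s *t* test for 2 independent samples". It assumes mean reductions of 5% and 15%, an SD of at most 15% in both arms and a 5% significance level. This leads to 35 per group for 80% power and 49 for 90%; 49 is chosen.
- Section F (Statistical analysis) states: "If data are distributed normally and present homoscedasticity, comparison between both groups will be performed with simple tools such as Student´s *t* test". The alternative is: "Otherwise, non-parametric tests will be used".
- Section B (Visit 1) states: "A photograph of the affected eye (or both in bilateral lesions) will be taken".

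No section names baseline area as a covariate. None says how two affected eyes are combined.

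**The concern.** Dividing by baseline is one way of using it, but a rigid one. On the log scale the ratio is log follow-up area minus log baseline area, which fixes the baseline slope at 1. When the two measurements are imperfectly correlated and equally variable, the best slope is r, which is below 1. The ratio then stays negatively related to baseline: lesions measured large at baseline tend to show smaller ratios. A two-group comparison leaves that variation in the error term.

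At stake are the width of the confidence interval and some power. A linear model with baseline as covariate recovers them from a measurement the trial already takes on every patient.

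**Working it through.** **1. The plan's own figure.** Inputs from Section E: difference 15 − 5 = 10 points, SD 15, two-sided alpha 0.05. The percentage reduction is 100 × (1 − ratio), so testing it is the same as testing the ratio.

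n per arm = 2 (z₀.₉₇₅ + z_power)² × 15² / 10²

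- 80% power: 35.3, rounded up to 36 (exact noncentral t: 37). Stated: 35.
- 90% power: 47.3, rounded up to 48 (exact noncentral t: 49). Stated: 49.

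The stated figures agree to within 2 per arm. Power at 49 per arm is 91.0% by the normal formula and 90.4% by noncentral t.

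**2. Gain from adjustment.** Let log area have SD S at both visits and correlation r.

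- Variance of the log ratio: 2S²(1 − r).
- Residual variance after regression on log baseline: S²(1 − r²).
- Relative variance: (1 − r²) / [2(1 − r)] = (1 + r)/2.

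Regressing the log ratio on arm and log baseline gives exactly the same arm effect as regressing log follow-up area on them. For changes of the size planned here the raw ratio is nearly linear in its log, so the ratio adjusted for log baseline should keep almost all of the gain.

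Example at r = 0.5: the multiplier is 0.75. The standardised effect at 49 per arm is 10 / (15 × √0.75 × √(2/49)) = 3.81, and power is Φ(3.81 − 1.96) = 96.8%.

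**3. Check by simulation.** The protocol's SD of 15 points implies log-ratio SDs of √ln(1 + (0.15/0.95)²) = 0.157 and √ln(1 + (0.15/0.85)²) = 0.175, with root mean square 0.166. Log-normal areas were simulated with this SD, 49 per arm, mean reductions of 5% and 15%, and 40,000 trials per setting.

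| r (assumed) | (1+r)/2 | n per arm, 90% power (formula) | Power at 49 (formula) | Simulated: ratio, t test | Simulated: ratio adjusted for log baseline |
|---|---|---|---|---|---|
| 0.50 | 0.75 | 36 | 96.8% | 90.2% | 96.2% |
| 0.65 | 0.825 | 40 | 95.3% | 90.3% | 94.5% |
| 0.80 | 0.90 | 43 | 93.6% | 90.4% | 92.9% |
| 0.90 | 0.95 | 45 | 92.3% | 90.1% | 91.1% |
| 0.95 | 0.975 | 47 | 91.6% | 90.3% | 90.8% |

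The simulated values are good to about one point, depending on how the log-normal model is calibrated. Simulated type I error was 4.9–5.2% for both methods at every r.

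**4. Where r might lie.** From 2S²(1 − r) = 0.166², r = 1 − 0.166²/(2S²). If S, the between-patient SD of log area, is 0.3 to 0.8 (assumed), r is about 0.85 to 0.98 and the variance saving (1 − r)/2 is only about 1–8%.

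**5. Why the outcome should stay a ratio.** Section A contemplates lesions being totally eliminated. The ratio is then 0, whereas log area is undefined without an added constant. With one complete regression on doxycycline and the rest as above:

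- Unadjusted t test: about 94% power.
- Ratio adjusted for log baseline: 94–98% across r.
- Log-area model with an offset of 1% of median area: about 60–65%.
- Log-area model with an offset of 0.1% of median area: about 16–20%.

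A single cure becomes an extreme outlier on the log scale, and the result then turns on an arbitrary constant.

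**The case against.** The strongest reply is that nothing here is an error. The comparison is randomised, regression to the mean acts alike in both arms, type I error is held, and the sample size is sound. The t test is conditional on checks of normality and variance, with a non-parametric alternative. The wording of Section F gives the t test as an example, so it does not strictly rule out a covariate, and a statistical analysis plan that is not shown may add one. If r is high, the gain is a point or two of power. All of this stands. What remains is that Sections C, E and F together describe an unadjusted comparison, and that the improvement costs nothing in data.

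A reader might infer three stronger claims that the protocol does not support:

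- **The baseline is wasted, or the estimate is biased.** The ratio does use baseline, and the unadjusted comparison is unbiased under randomisation. Adjustment improves precision and accounts for chance imbalance in the sample actually drawn.
- **Type I error is inflated because both eyes are photographed.** If eyes were entered as independent observations, an assumed 30% bilateral share and inter-eye correlation of 0.5 would give a variance factor of 1 + 2(0.3)(0.5)/1.3 = 1.231 and a type I error of about 7.7%. But Section E gives each patient a single number and counts the sample in patients, so the protocol does not plan that analysis. Only the rule for forming the number from two eyes is unstated.
- **The trial is badly underpowered without adjustment.** That would need more noise than the SD of 15 that Section E sets as a maximum.

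**Conclusion.** The point holds as a recommended efficiency improvement, not as a defect that invalidates the test or the sample size. With an SD of 15 and 49 per arm, adjusting the ratio for log baseline area lifts power from about 90% to about 96% if r = 0.5, 95% if 0.65, 92–93% if 0.8 and 91% if 0.9 to 0.95, with type I error near 5% throughout. These figures assume log-normal areas, equal log-area variance at both visits and the Section E effect and SD. The value of r is not in the protocol, and the plausible gain runs from under one point to about six. The bilateral question is a minor clarification.

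**What to change.** In Sections C and F:

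- Keep the ratio (equivalently the percentage change) as the main outcome, so that a fully regressed lesion counts as 0.
- Replace the unadjusted t test as the primary comparison with a linear model of the ratio on arm and log baseline area, and report the adjusted arm difference with its 95% CI. The non-parametric comparison already foreseen can remain as a sensitivity analysis.
- Do not make log follow-up area with an added offset the primary analysis.
- Add one sentence on bilateral disease saying how the two eyes give the single value per patient, for example the mean of the two ratios, with the baseline covariate averaged over the same eyes.

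The cost is a few sentences and a few lines of code. No new data, visits or patients are needed, and the planned 98 patients need not change.
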